## Study objectives

### Hypotheses and outcomes

#### Primary hypothesis and expected outcomes

We anticipate cognitive far transfer effects following OC and, to a lesser degree following VA exhibited by improved EF performance, particularly auditory and visual WM performance during fMRI tasks, as compared to the CG. We expect greater improvement in OC except for visual WM.

#### Secondary hypotheses and expected outcomes

We foresee that OC interventions will be associated with increased functional and structural brain plasticity as compared to VA and the CG (OC > VA > CG), notably in a set of temporal (medial and lateral (auditory)), prefrontal, and superior parietal areas, as well as in the basal ganglia (striatum), the cerebellum and the corpus callosum, supporting WM, EF and attention [24, 35, 73, 75].

We also anticipate greater Functional Connectivity (FC) changes following the same gradient (OC > VA > CG) in the Default Mode Network (DMN), Central Executive Network (CEN) and Salience Network (SN) [76, 77], in conjunction with increased or decreased structural connectivity [78]. In addition, plasticity associated with VA might occur specifically in the visual cortex.2)We hypothesize that we can model child EF development over two years in primary school children (initially 6-8 YOA) using multivariate data-driven analyses (see Statistical analysis plan and sample size calculation Planned statistical analyses, Step 3) that take into account all behavioral and brain data at all three time points, across the three experimental conditions (OC vs. VA vs. CG).

### Primary and secondary endpoints

Primary Endpoint: Improve WM performance through OC and to a lesser extent through VA interventions, as assessed by psychometric testing and fMRI tasks, in primary school children of 6-8 years at the start, following them over two years of intensive OC vs. VA group-interventions, as compared to baseline data (representing progress) and to the CG data (representing natural development). The rationale for the selection of WM was explained in *1.3.2.*

Secondary Endpoints:Identify significant changes in structural and functional brain plasticity, i.e. biomarkers (brain features), comparing 1-year and 2-year values to baseline values (i.e. progress) of both art interventions and to the CG values (natural development).Establish significant correlations between brain plasticity and EF performance change, comprising WM, following the two interventions, particularly MIP (OC), after one and two years of interventions, compared to baseline and to the CG values.Create a comprehensive data-driven model of child interrelated brain and EF development over the first two years of their academic curriculum, with and without additional cognitive enrichment (OC vs. VA vs. CG).Within the context of this comprehensive model of EF, explore how artistic enrichment may influence the typical transition from a more unified to a more multifaceted EF structure around age eight, comparing these findings against a minimally enriched CG [18, 20].

*Baseline factors* that may influence the endpoints are, amongst others, age, gender, socioeconomic background, and WM performance at baseline. These confounding factors will be partially controlled for through the stratified randomization and also in the statistical analyses (by means of covariates).

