**Table 2 Tab2:**
[figure not shown]
Study procedures with timelines

Baseline (T0) testing will begin approximately six weeks before the onset of the interventions for both art groups. All intervention groups will receive 1 hour and 30 minutes of art lessons per week, during two full years, outside school hours. The mid-intervention testing will take place after one full year of interventions. Final testing will take place after two years of interventions.

Total duration for an average child to participate in the study will therefore take approximately two years and three months (may vary as a function of the dates of screening and testing before and after the interventions), within a period stretching from December 2023 till end of August 2026, depending on which wave the child participates in.

We will cope with test-retest effects by 1) using different versions, or different items, or different order of items of the tests at T0 (baseline, before the interventions), at T1 (after one year of interventions) and at T2 (after two years of interventions), and 2) by considering the test-retest effects in the control group between time points. This also holds for the fMRI visual and auditory WM tasks.

For the behavioral battery, we will adhere to the rule of two tests for each assessed function, primarily choosing tests that have been validated in our target population.

At each time point (T0. T1, T2) a behavioral battery (2x60 minutes at different days) and an MRI battery (45 minutes of measurement, plus 45 minutes of preparation) will be passed by each child.

The behavioral battery primarily focuses on EF, with a special emphasis on WM as the main outcome. Testing of all EF functions is done via at least two different tasks. However, we will also evaluate emotion regulation (ER), which is supposed to be closely associated with EF performance [84–86]. One test on prosocial tendencies [84] is also included. ER and prosocial behavior may be reinforced by group training. We will also evaluate potential direct transfer from the group art courses: musical (OC) [87, 88] and visuospatial capacities (VA) [89].

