In the 2^nd^ axis (individual prediction), we will attempt to predict the difference in behavioral outcomes (digit span, auditory/tonal, and visual WM) from the difference in connectomes^3^ between time points T0 and T2. The control group will allow discarding developmental connectivity differences that are not related to our interventions or not meaningful for predicting working memory. Here, we will leverage recent advances in graph-based machine learning, particularly graph neural networks (GNN). We will use each subject’s connectivity values (either in the whole brain, or in specific functional networks of interest (CEN, SN)) as input to train a GNN model to predict the behavioral scores. The scores can be predicted one by one, or jointly by using a multi-output network (see Fig. 1 for an overview of the analyses). To improve performance, we will use a technique called *transfer learning*, by pre-training the GNN model using related tasks and scores from other cohorts, and then fine-tune using our own data. The team of [name] successfully developed related transfer learning approaches on other datasets. Further, we will use our newly developed graph data augmentation technique^4^ to ensure that sample size is not an issue. Using a GNN model allows us to perform this analysis for both the structural and functional connectomes, where functional connectomes are obtained either from resting-state or from task-based connectivity.

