**Fig. 1 Fig1:**
[figure not shown]
Data analysis overview This table summarizes steps and methods used to achieve our ultimate goal i.e., the prediction of the main behavioral outcome: working memory improvement and development (WM: working memory; ANCOVA: Analysis of Covariance; LME: linear mixed model equations; GLM: general linear model; MRI: magnetic resonance imaging; ICA: independent component analysis; ICAPs: innovation-driven co-activation patterns, PLS: partial least squares; GNN: graph neural networks)

Significance level will be strictly controlled using false discovery rate special techniques for multiple comparison correction for univariate and multivariate analyses involving behavioral, MRI and combined behavioral and MRI data [117].

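### The primary outcome is stated in two different ways and covers several working-memory scores and contrasts, and the stated false discovery rate control does not hold the primary false-positive risk at 5%

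*Protocol article*

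**What the plan says.** The article describes the primary outcome in several places.

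- **Primary and secondary endpoints:** "Improve WM performance through OC and to a lesser extent through VA interventions, as assessed by psychometric testing and fMRI tasks", followed by "as compared to baseline data (representing progress) and to the CG data (representing natural development". OC is placed above VA for WM as a whole, with no exception.
- **Primary hypothesis and expected outcomes:** the benefit is to be "exhibited by improved EF performance, particularly auditory and visual WM performance during fMRI tasks, as compared to the CG". On OC against VA it adds: "We expect greater improvement in OC except for visual WM".
- **Study procedures with timelines:** the behavioral battery focuses on executive functions "with a special emphasis on WM as the main outcome".
- **Planned statistical analyses, Step 3, second axis:** the WM scores are listed in the aim to "predict the difference in behavioral outcomes (digit span, auditory/tonal, and visual WM".

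Step 2 of the same section fits a linear mixed model to each behavioral variable separately, across the three groups and two years. The sample size section takes WM as the main behavioral outcome and sizes a simple between-group comparison at alpha 0.05 and power 0.80, which gives 48 children in total, 24 per group. On multiplicity, the paragraph after Fig. 1 says: "Significance level will be strictly controlled using false discovery rate special techniques for multiple comparison correction". It applies this to univariate and multivariate analyses of behavioral, MRI and combined data, and sets out no family and no separate protection for the primary endpoint.

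**The concern.** The two statements differ in scope (executive functions with emphasis on two fMRI tasks, against WM from psychometric and fMRI tasks). They also differ in prediction for visual WM. If VA matched or exceeded OC on the visual n-back, the result would fit the hypothesis section and run against the endpoint section. Neither names a score, a visit or an ordered contrast, so success could be declared on any of several results.

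The stated safeguard does not close that gap. FDR limits the expected share of false rejections among all rejections. It does not limit the probability of at least one false rejection among the primary tests, unless no hypothesis in the family is truly non-null. At stake is whether a positive WM finding carries the 5% error rate that readers will attach to a primary result, and that the sample size calculation assumes.

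**Working it through.** **1. The plan's own figure.** The effect size and sidedness behind 24 per group are not given, so the figure can only be solved backwards. With a two-sample t-test, two-sided alpha 0.05 and 80% power, n = 24 per group implies a standardized difference d of about 0.83 (0.73 if one-sided). The attrition step reproduces: 35 / (1 − 0.30) = 50. At d = 0.83 and 35 per group, one unadjusted test has about 93% power.

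**2. How many primary tests.** There are three WM scores (digit span, tonal, visual), or four if forward and backward digit span are counted apart. OC vs CG and VA vs CG give 3 × 2 = 6 tests at one visit. Adding OC vs VA gives 3 × 3 = 9.

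**3. What FDR does to a null primary test.** Benjamini-Hochberg (BH) rejects p-values up to q × k / m, where k is the number rejected and m the family size. If S strong effects elsewhere are all rejected, the smallest null primary p-value needs only to fall below q × (S + 1) / m. For P independent null primary tests, the chance of at least one false rejection is then about 1 − [1 − q(S + 1)/m]^P.

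With q = 0.05 and P = 9:

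| Strong effects S | Other nulls | m | Threshold | Formula | Simulation |
|---|---|---|---|---|---|
| 0 | 0 | 9 | – | – | 5% |
| 5 | 0 | 14 | 0.05 × 6/14 = 0.0214 | 17.7% | 17% |
| 10 | 0 | 19 | 0.05 × 11/19 = 0.0289 | 23.2% | 23% |
| 15 | 0 | 24 | 0.05 × 16/24 = 0.0333 | 26.3% | 25–26% |
| 5 | 20 | 34 | 0.05 × 6/34 = 0.0088 | 7.7% | about 8% |
| 10 | 20 | 39 | 0.05 × 11/39 = 0.0141 | 12.0% | 12% |
| 15 | 20 | 44 | 0.05 × 16/44 = 0.0182 | 15.2% | 15% |

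The simulations take each strong effect as a z-shift of 4, an assumption. At 35 per group that is d = 4 × √(2/35) = 0.96.

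**4. Correlated scores and shared arms.** For three scores with correlation 0 to 0.5 and contrasts built from the same three arms, simulation gives:

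- No true effect anywhere: 4–5%.
- BH within the WM tests only, OC truly working on one or two scores (correlation 0 or 0.3): 7.5–9.5% with two contrasts, 10–12% with three.
- BH pooled with 10 true and 10 null other outcomes: 11–12% with two contrasts, 13–14% with three.
- BH pooled with 20 true effects and no other nulls: 18–20% with two contrasts, 22–25% with three.

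**5. Link to sample size.** Bonferroni over six tests uses 0.05/6 = 0.0083. At d = 0.83 this needs about 38 per group, and 35 per group gives about 77% power for each test. Over three tests (0.05/3 = 0.0167), 35 per group gives about 84%.

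**The case against.** The endpoint section can be read as a general gradient for WM, with the hypothesis section refining it for one modality. Most of the article treats WM as the main outcome, which goes far towards settling executive functions against WM. The list of three WM scores comes from an exploratory prediction step, not from an endpoint definition. An article may also leave the definition of the FDR family to an analysis plan that is not shown. These points lessen the conflict but do not remove it. The two primary statements still disagree on visual WM and on scope, and the claim of strict control is made in this document.

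Three stronger readings are tempting and are not supported.

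- **That a false primary claim has a 17–26% chance under this plan.** Those values need nine independent null primary tests pooled with 5 to 15 strong effects and no other nulls. The article does not say that everything is pooled, and it examines behavioral and brain data separately in Step 2. The battery also holds many other outcomes that could be null, which lowers the figure. Brain maturation shared by all arms would add true effects only if time effects were part of the family.
- **That the tests go uncorrected.** The article plans a correction, so error rates for unadjusted testing do not describe it.
- **That both follow-up visits are primary, doubling nine tests to 18.** The primary endpoint speaks of two years, only the secondary endpoints name the one-year values, and the Attrition / drop-outs section sets its target at T2.

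**Conclusion.** The point stands in a limited form. The primary outcome is stated inconsistently and spans at least three scores and two or three contrasts, against a sample size built on one comparison. Describing FDR as strict control of the significance level is wrong for a primary claim.

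The size cannot be fixed from the document, because it depends on which tests share a family and how many of them are truly non-null. The chance of a false primary claim is at or below about 5% if nothing is real. It is about 7–12% if FDR is confined to three WM scores and OC works on some of them. It reaches about 25% only if WM tests are pooled with many strong effects and few other nulls. All of these figures assume BH at q = 0.05. This should be corrected, but it does not by itself invalidate the design.

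**What to change.** 1. Reconcile the primary hypothesis with the primary endpoint, including whether visual WM is exempt from the OC-over-VA prediction.
2. Name the primary WM score, or a short list, together with the visit and the contrasts. T2 fits the retention target in the Attrition / drop-outs section. The choice of score belongs to the sponsor; Digit Span Backward is only one possibility.
3. Test these with familywise control at two-sided 0.05. One option is a fixed sequence, OC vs CG and then OC vs VA, which leaves the first contrast at the full 0.05 that the sample size assumed if that figure was two-sided. Another is Holm over the short list.
4. Confine FDR to secondary outcomes, in families kept apart from near-transfer and brain outcomes, and reword the sentence on strict control.

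The cost is wording in the protocol and analysis plan and a registry update. Some WM scores or contrasts lose primary status. Under Holm they stay primary but face a stricter threshold: with six tests, the first step has the power of about 77% shown above, against 93% for a single test.

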## Methods and design

### Study design

The proposed study is a 1) randomized (stratified), 2) three-arm, 3) open, 4) monocentric (primary schools in Geneva) 5) national (Switzerland) 6) intervention study.

Stratified randomization will be applied to compose equivalent groups, stratifying for the factors 1) age, 2) gender, and 3) socio-economic background to balance all groups for those factors.

3-arm design: one experimental group (OC), another art group (VA), and an active control group (CG). The study design is open, as the assigned group cannot be blinded. Blinding will only be applied at the randomization level and, when possible, during the statistical analyses.

However, participants in all groups will be ignorant of the more robust hypotheses for brain and behavioral plasticity for the OC and, to a lesser degree for the VA group. We will explain to the parents and their children that we will compare the potential impact on intellectual child development, following two distinct art interventions or cultural outings.

The psychometric battery consists exclusively of validated tests.

A full list of the psychometric battery tests and MRI measurements can be found in Tables 3 and 4 in section "Study procedures with timelines". Importantly, each EF construct is measured by multiple tests.

We will cope with test-retest effects by 1) using different versions, or different items, or different order of items of the tests at T0 (baseline, before the interventions), at T1 (after one year of interventions) and at T2 (after two years of interventions), and 2) by taking into account the test-retest effects in the CG between timepoints.

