#### Randomization procedure

To assure homogeneity of the groups at the start, we will apply a stratified randomization into OC, VA and CG groups, via a stratified procedure according to the factors 1) age, 2) gender 3) socio-economic background. We will apply a clustering procedure, to obtain the closest triplets of participants, based on the three stratification factors. Then we will randomly attribute one child of each triplet to OC, VA or CG groups. Stratified randomization may increase statistical power while retaining the benefits of random allocation [82]. We applied very similar randomization methods in the past [83].

We will not reveal our specific hypotheses regarding the various interventions to the families and art teachers. Instead, the research will be presented as an assessment of child development following different art courses and cultural outings, which accurately reflects the study's nature.

If we receive more applications than necessary, we will attempt to achieve gender balance. However, as no scientific documentation exists that boys or girls would be advantaged for music practice or visual arts learning, an imbalance of gender is not a major issue. Following the stratified randomized procedure, girls and boys will be evenly distributed over the groups.

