Finally, we will also employ the International Matrix Test [90], to assess speech in noise perception abilities, which are known to improve with musical training in children [43, 91]. Improvements in speech perception, especially in noisy environments, can significantly enhance school performance and everyday communication [43], thereby positively influencing daily life functioning and academic success.

To avoid order effects, the different tests in the behavioral battery are carried out in two distinct sequences, counterbalanced between the children in each group. The alternation of difficult and simple tasks is balanced in each sequence.

The detailed behavioral and MRI batteries are depicted in Tables 3 and 4.

**Table 3 Tab3:** Behavioral data collected at all time points. Total testing duration 2*60 minutes, without the fMRI tests and judgements/ratings. It comprises testing of all main EF components using mainly the WISC: Wechsler intelligence scale for children–5th Edition [89] and the KiTAP: Test of Attentional Performance for children [92]

COGNITIVE DOMAIN	FUNCTION	NAME OF THE TEST	BRIEF DESCRIPTION	REF.
Music abilities	Rhythm perception	Intermediate Measures of Music Audiation (IMMA)	Pattern comparison, judge if same or different in rhythm RIGHT button for identical patterns, LEFT for different patterns	[87, 88]
Visuo-spatial abilities	1. Visuo-spatial reasoning & praxis 2. Problem solving	Cubes test (WISC-V)	Arranging physical pictured cubes in specific patterns according to a design	[89]
Working memory (fMRI)	Auditory tonal working memory	Pattern comparison (inspired by IMMA)	Compare two 3-note sinus tone patterns 1. Low load condition (3 identical notes): RIGHT button for identical patterns, LEFT for different patterns 2. High load condition (3 different notes): RIGHT button for identical patterns, LEFT for different patterns	Adapted from [87, 88]
	Visual-spatial working memory	Visual n-back	6-case spatial matrix containing appealing monster figures - conditions: 0-back, 2-back Right button for matched n-back trial l, LEFT button for unmatched n-back trial	[93]
Memory Systems	Short-term memory	Digit Span Forward (WISC-V)	Repeating series of digit sequences of increasing length aloud	[89]
	Working memory: information manipulation	Digit Span Backward (WISC-V)	Repeating series of digit sequences of increasing length aloud backwards	[89]

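### Blinding is confined to randomization and analysis, so T1 and T2 testers and scorers of Digit Span Backward may know the child's arm although they could be kept unaware of it

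*Protocol article*

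**What the plan says.** Under Study design the article gives the reason for openness, "The study design is open, as the assigned group cannot be blinded", and then says where blinding applies: "Blinding will only be applied at the randomization level and, when possible, during the statistical analyses". Testing and scoring of outcomes are not on that list.

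The hypotheses are withheld from some people. Study design says that "participants in all groups will be ignorant of the more robust hypotheses for brain and behavioral plasticity for the OC", and Randomization procedure adds: "We will not reveal our specific hypotheses regarding the various interventions to the families and art teachers". Neither section mentions the staff who test the children.

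WM is the primary endpoint, "as assessed by psychometric testing and fMRI tasks" (Primary and secondary endpoints). Study procedures with timelines describes the behavioral battery as one "with a special emphasis on WM as the main outcome". In Table 3 the only test outside the scanner that carries the working-memory label is Digit Span Backward: "Repeating series of digit sequences of increasing length aloud backwards". The individual-prediction part of Step 3 (Planned statistical analyses) names the WM outcomes as "digit span, auditory/tonal, and visual WM".

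**The concern.** The protocol draws a conclusion about all outcome-stage blinding from a fact about participants. A child who goes to orchestra class knows it, and so do the parents and the teacher. It does not follow that the person who tests the child a year later must know it.

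The plan takes expectancy seriously elsewhere: it withholds the hypotheses from families and art teachers, and it uses independent judges to rate videos and artwork. Those ratings measure learning in the trained domain. The article describes no comparable protection for the spoken WM test, which belongs to the primary endpoint.

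A spoken span test leaves some room for tester influence through pacing, encouragement and the handling of doubtful answers. If such influence differs by arm, it biases the comparison that the trial exists to make.

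**Working it through.** **1. Is the gap stated, or merely left out?** It is stated. The blinding sentence restricts itself with the word only, so outcome testing lies outside it. No other section of the article provides for a masked tester, a masked scorer or coded recordings for the WM tests.

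**2. Does the reason cover testers?** No. It concerns who can know the assignment by taking part. Testers and scorers take no part in lessons or outings unless they are rostered to.

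**3. Which WM measures are exposed?**

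| WM measure (Table 3) | Response | Room for tester or scorer influence |
|---|---|---|
| Digit Span Backward | Spoken | Some |
| Tonal pattern comparison (in scanner) | Left or right button | Less |
| Visual n-back (in scanner) | Left or right button | Less |

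That an examiner delivers Digit Span is inferred from the spoken format; the article does not say so.

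**4. Where would a bias appear?** Baseline testing precedes the interventions, so expectancy tied to the arm would arise at T1 and T2. Step 2 compares the three groups over time, and that contrast would absorb it. The planned safeguards act on other problems:
- Alternate versions and allowance for the control group's test-retest gain deal with practice effects, not with a shift that differs by arm.
- Masking the analyst does not change scores that are already recorded.

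**5. In which direction?** The primary hypothesis expects orchestra (OC), and to a lesser degree visual arts (VA), to exceed the control group (CG), with OC ahead except for visual WM. Digit span is on the favoured side.

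**6. Size (illustration only).** The documents give no tester shift, so b is assumed.
- Inputs from the sample-size section: alpha 0.05, power 0.80, 24 per group needed, 50 enrolled per group, 30% attrition.
- Attrition check: 50 × 0.70 = 35 per group, which agrees with the article.
- The effect size behind 24 per group is not stated. Back-solving a two-sample t-test gives d ≈ 0.83 two-sided (0.73 one-sided).
- With no true effect and n = 35 per arm, the t statistic has noncentrality b × √(n/2) = b × √17.5 = 4.183 × b on 68 degrees of freedom.

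| Assumed shift b (SD) | Noncentrality | Two-sided rejection rate | b as share of d = 0.83 |
|---|---|---|---|
| 0 | 0 | 5% | 0% |
| 0.1 | 0.42 | 7% | 12% |
| 0.2 | 0.84 | 13% | 24% |
| 0.3 | 1.25 | 24% | 36% |

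This is a simple two-arm comparison at one time point, not the planned mixed model with multiplicity control. It shows only that a modest shift would matter.

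**The case against.** The strongest reply is that the article never says who tests the children or what those staff know, and that tester staffing is a detail a condensed article may leave to the full protocol. The first part stands. A reader might infer that staff who know both the arm and the hypothesis will run the tests. The documents do not support that; they only provide nothing to prevent it. The second part does not dispose of the point, because the article does not leave blinding open: it names the stages where it applies and leaves testing out.

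A reader might also infer that the whole primary endpoint is compromised. It is not. Two of the three WM measures are button-press tasks, and the primary hypothesis stresses those. They also give a partial check on a digit-span result, though an imperfect one, since they measure different modalities. Nor does the exposure extend evenly over the other Wechsler tests: matrix reasoning and figure weights are answered by choosing among options, and they are not WM tests.

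The ordering OC > VA > CG should not be quoted as the WM hypothesis. It is written for brain plasticity and connectivity, while the WM hypothesis makes an exception for visual WM.

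Finally, one could set an assumed shift against the meta-analytic g of 0.26 cited in the Background: 0.1/0.26 = 38% and 0.2/0.26 = 77%. Those percentages are not evidence. The shift has no source in the documents, and that g pools cognitive skills and academic achievement over short-term studies.

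**Conclusion.** The point holds in a limited form. The article restricts blinding to randomization and analysis for a reason that does not apply to testers and scorers, and it describes no other protection for Digit Span Backward at T1 and T2. An arm-dependent tester effect is possible. It would fall into the group-by-time contrast, and it would probably favour OC and, less so, VA over CG.

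Whether such an effect will occur, and how large it would be, cannot be established from the documents. The 7% to 24% range rests on assumed shifts of 0.1 to 0.3 SD and a simplified test. The conclusion also assumes that an examiner gives and scores Digit Span. This is an inexpensive improvement to make before T1 and T2 testing, because masking that was absent at testing cannot be restored afterwards. It changes no arm, visit or sample-size figure.

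**What to change.** Amend the blinding statement under Study design to say that, where feasible:
- existing staff who test and score at T1 and T2 have no access to the allocation list and do not run that child's lessons or outings;
- children and families are asked before each session not to mention their group;
- testers record any suspected unblinding, and its frequency is reported by arm.

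As an option, Digit Span may be scored from coded recordings by a team member unaware of arm. Masking to visit should not be required, because versions, items or item order differ between time points and may reveal it. The recruitment section describes consent to MRI recordings and to filming of courses, not to recording of test sessions, so this option depends on consent covering it or being extended.

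The cost is some rostering effort, plus recording and possibly a consent change if the option is used. The article does not describe the testing team, so whether present staffing suffices has to be confirmed. Some children will reveal their arm, so masking will be partial and should be reported as such.
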